### Protocol violation

Lost to follow-upTreatment crossover outside the pre-defined interval for early crossover surgery

Patients that meet any of these criteria will remain in the study and be included in the intention-to-treat analysis but omitted from a per-protocol analysis.

### Participant withdrawal

If the patient withdraws the consent, patients will be included in the statistical analysis through multiple imputation, if baseline data is obtained, otherwise imputation is not possible, and the patient will be replaced to meet the calculated sample size.

### Blinding

The trial will consist of several levels of blinding:The primary outcome will be blinded to everyone involved in the trial, apart from the patients and a central trial worker (non-physician), who will only review the questionnaire for completion in REDCapThe statistical analysis will be conducted by a blinded biostatistician

### Outcome timepoints

Subjective and objective outcome measures will be obtained at the following time points: pre-injury, baseline, 6 weeks, 12 weeks, 26 weeks, 52 weeks, 2 years, and 5 years.

### Baseline data

The following baseline data will be collected after enrollment: age, sex, height, weight, arm dominance, American Society of Anesthesiologists (ASA) grade, pre-injury UCLA activity score [37], list of current diagnosis and medication, mechanism of injury, radiological variables (AO/OTA and fracture location), previous surgery to the arm, tobacco and alcohol habits, employment and educational status. DASH and European Quality of Life – 5 dimensions (EQ-5D-5L) questionnaires will be sent by REDCap immediately after randomization to obtain pre-injury scores.

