### Recruitment

Patients admitted to the emergency department (ED) in any of the trial sites will be clinically examined and plain radiographs will be obtained to confirm the diagnosis. If the patient fulfills the eligibility criteria, they will be informed of the trial by staff and receive written information with patient participation information and “Researchers rights in a health science research project.” They will be given time to consider and will be scheduled for an appointment with research staff within 10 days. If written consent is obtained at the consultation, randomization will occur immediately after.

Patients will be provided with transport allowance to cover the costs for consultations at 26 weeks and 52 weeks. They further accept telephone calls if they miss follow-up visits to promote participant retention and complete follow-up.

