### Randomization

A computerized database software, Research Electronic Data Capture (REDCap)© [38] will be used to generate an irreversible random allocation sequence and perform block randomization with selected block sizes of 2 and 4, which will be stratified on site and age (18–64 and +65). Patients will be assigned to the trial with an allocation of 1:1 to either surgical treatment or non-surgical treatment. The trial worker acquires the allocated treatment from the central coordinator with randomization rights to REDCap. The trial worker then initiates the treatment, either by scheduling the surgery date or applying the chosen non-surgical method.

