### Primary outcome measure

The primary outcome is the DASH score at 52 weeks [3]. The DASH will also be assessed at pre-injury, 6, 12 and 26 weeks, and 2 and 5 years. The DASH score is a 30-item self-reporting patient-reported outcome measure specific for physical function and symptoms of the upper limb. Scores range from 0 (no disability) to 100 (most severe disability). The DASH score is validated for the target population [39] and has undergone cross-cultural adaptation in Danish, Swedish and Norwegian [40].

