### Secondary outcome measures

Secondary outcomes consist of the DASH score, a self-reported measure of health-related quality of life (EQ-5D-5L), complication rates, visual analog scale (VAS) for pain from the arm, a functional outcome score (Constant-Murley), and anchor questions including clinical anchors, retrospective global transition questions and a binary repeat treatment question. Secondary outcome measures will be assessed at baseline, 6 weeks, 12 weeks, 26 weeks, and 52 weeks (Fig. 3):DASH score at earlier timepoints than 52 weeks (MIC [39], 7 and 10 respectively to age 18–64 and 65+)General health status questionnaire measured by EQ-5D-5L [41] (MIC [42], 0.074)Complications after treatment will be recorded and include local complications, early general complication, and mortality:Local complications: Infection (needing antibiotic treatment with or without debridement), nerve or vascular injury, surgical revision (due to implant malpositioning, hardware failure, aseptic loosening, or peri-implant fracture), and tolerance problems with a brace (discomfort resulting in non-compliance of wearing the braceEarly general complications needing hospitalization within 12 weeks from primary and secondary treatment [43, 44]:Major adverse cardiac events (MACE) including myocardial infarction, heart failure, cardiomyopathy and cardiac arrythmias.Other major adverse events include all-cause hospitalization other than the defined MACE.MortalityPain is assessed by using VAS. Patients are asked to assess their overall pain from the arm from 0 to 100 in a day (MIC [45], 16.55mm)Constant-Murley score [46] (MIC [39], 6.1). The subscales of strength and range of motion (ROM) will be depicted. ROM (flexion-extension) of the elbow will be recordedClinical anchor (CA) questions were presented with 5 response options (RO) and analyzed as a 5-point Likert scale:

Q: In general, would you say your health is?RO: Excellent, Very good, Good, Fair, Poor
*Q: How would you describe the results of the (operation/non-surgical treatment)?*
RO: Excellent, Very good, Good, Fair, Poor
*Q: How would you describe the function of your upper arm?*
RO: Excellent, Very good, Good, Fair, Poor
*Q: How would you describe the pain from your upper arm?*
RO: None, Mild, Moderate, Severe, ExtremeRetrospective global transition questions (RGTQ) presented with 5 response options and analyzed as a 5-point Likert scale:

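### Recalled pre-injury DASH and EQ-5D-5L are collected after open-label allocation: the primary week-52 comparison is safe, but baseline comparability and change-from-pre-injury estimates are exposed

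*Protocol article*

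**What the plan says.** All of this is in the protocol article.

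- **Recruitment:** "If written consent is obtained at the consultation, randomization will occur immediately after". No questionnaire step is described between consent and allocation.
- **Randomization:** "The trial worker then initiates the treatment, either by scheduling the surgery date or applying the chosen non-surgical method". The patient therefore learns the arm at once.
- **Blinding:** "The primary outcome will be blinded to everyone involved in the trial, apart from the patients and a central trial worker". Patients know their treatment.
- **Baseline data:** the DASH and EQ-5D-5L "questionnaires will be sent by REDCap immediately after randomization to obtain pre-injury scores". No return date before treatment is stated. The other baseline items, including the pre-injury UCLA activity score, come under a different phrase: "The following baseline data will be collected after enrollment: age, sex, height, weight, arm dominance".
- **Primary outcome measure:** "The DASH will also be assessed at pre-injury, 6, 12 and 26 weeks, and 2 and 5 years". In this list nothing but the pre-injury score precedes 6 weeks.
- **Secondary outcome measures:** "Secondary outcome measures will be assessed at baseline, 6 weeks, 12 weeks, 26 weeks, and 52 weeks". Outcome timepoints likewise names pre-injury and baseline separately. The text does not place the baseline assessment before or after randomization.
- **Primary analysis and Secondary analysis:** the primary outcome is analysed by univariable linear regression. The imputation and adjusted models use age, sex, smoking, alcohol, UCLA activity and ASA grade. A mixed model with modality, time and their interaction is fitted to the longitudinal observations, without listing the time points.
- **Cost-effectiveness:** EQ-5D supplies the utilities for quality-adjusted life-years over one year.

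**The concern.** Pre-injury function is a subjective recollection. Here it is requested from a patient who knows the arm and who, with no deadline, may answer after treatment has begun. Satisfaction or disappointment with the allocation, or the early experience of surgery or a brace, can change how the earlier state of the arm is remembered. If it does so differently in the two arms, the recorded score is no longer a true baseline, because it carries an effect of allocation.

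Two things are at stake. First, an arm difference in pre-injury scores would look like failed randomization and could not afterwards be told apart from chance imbalance. Second, any estimate expressed as change from pre-injury inherits the recall difference. Neither can be repaired in the analysis once the data are in. The Discussion shows that the authors care about influence on answers, since patients complete the DASH before seeing the physician. The pre-injury score has no matching safeguard against knowledge of the arm.

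**Working it through.** **1. Order of events.** Consent, then immediate randomization, then open start of treatment, then dispatch of the pre-injury questionnaires. That the patient knows the arm when answering is an inference, but a firm one from Recruitment, Randomization, Blinding and Baseline data read together.

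**2. The plan's own figures.** The point disputes no figure; the sample sizes are inputs. With two-sided alpha 0.05 and power 0.80, n per arm = 2 × [SD × (1.960 + 0.842) / difference]².
- SHAFT-Y: SD 14.91, difference 7 gives 71.22 per arm, 142.44 in total; × 1.15 = 163.8 (stated 163).
- SHAFT-E: SD 18.59, difference 10 gives 54.25 per arm, 108.50 in total; × 1.15 = 124.8 (stated 124).

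After 15% attrition the analysed numbers per arm are 163 × 0.85 / 2 = 69.3 and 124 × 0.85 / 2 = 52.7.

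**3. Which planned analyses contain the score.**

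| Analysis | Uses recalled score? | Effect of an arm difference s in recall |
|---|---|---|
| Primary: univariable week-52 DASH | No | 0 |
| Adjusted regression and imputation | Not DASH or EQ-5D; UCLA yes | Only through UCLA, if taken after allocation |
| Mixed model, week-52 contrast, categorical time | If pre-injury is a time point | Essentially 0: the shift is absorbed by the arm's own pre-injury mean |
| Mixed model, modality-time coefficient against pre-injury | If pre-injury is a time point | The full s |
| One-year QALY | If recalled EQ-5D is the starting utility | s × (6/52) / 2 |

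I checked rows three and four on simulated data with some week-52 values missing. Adding 5 points to one arm's pre-injury scores left the week-52 contrast unchanged and moved the interaction coefficient by exactly 5. If time were fitted as a straight line, the separation would not be this clean; the protocol does not say which is meant.

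**4. Size for a change-from-pre-injury coefficient.** Assumptions, none of them in the documents: s = 1 to 5 DASH points, correlation r between pre-injury and week 52 of 0.2 to 0.6, equal SDs, no true effect. SE = SD × √[2(1 − r)] × √(2 / n per arm), and type I error = P(|Z + s/SE| > 1.985), where 1.985 belongs to the final level of 0.0471.
- SHAFT-Y: SE = 3.20 (r = 0.2) to 2.27 (r = 0.6).
- SHAFT-E: SE = 4.58 to 3.24.

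| s | SHAFT-Y type I error | SHAFT-E type I error |
|---|---|---|
| 0 | 0.047 | 0.047 |
| 1 | 0.06 to 0.07 | 0.05 to 0.06 |
| 2 | 0.09 to 0.14 | 0.07 to 0.09 |
| 5 | 0.34 to 0.59 | 0.19 to 0.33 |

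The Secondary analysis section judges coefficients at 0.05, not 0.0471. At 0.05 every entry is higher by at most about 0.01.

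**5. Size for the QALY.** With a trapezoid over weeks 0 to 6 and an assumed utility shift of 0.02 to 0.074 (the latter being the protocol's minimal important change): 0.02 × 6/52/2 = 0.001 and 0.074 × 6/52/2 = 0.004.

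**The case against.** The strongest reply is that no named model uses the pre-injury DASH or EQ-5D-5L as a covariate, and no change-from-pre-injury DASH analysis is announced. That stands, and it rules out several stronger readings.

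- **That the primary result is biased.** A reader might infer this because the DASH is the primary outcome. The primary analysis compares week-52 scores without any pre-injury term, so its bias from this source is zero.
- **That the adjusted effect moves by slope times recall difference.** This would follow if week-52 DASH were adjusted for pre-injury DASH. No section plans that, so a figure of this kind set against the 7- or 10-point target would describe an analysis the trial does not propose. Nor is it the right formula for the mixed model, where the effect is either nil (week-52 contrast) or the whole difference (change coefficient).
- **That UCLA is certainly recorded after allocation.** Enrollment is not the same word as randomization, and the same section uses the latter for the DASH and EQ-5D-5L. The text leaves the order open.
- **That the trial has no other pre-treatment reference at all.** A separate baseline assessment is named and the schedule figure is not shown. The statement is safe only for the explicit DASH list.

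It can also be said that the mixed model's time points belong in the statistical analysis plan. That is fair, which is why the effect on this model is stated conditionally. What the reply does not answer is the order of collection itself, which the protocol fixes.

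**Conclusion.** The point holds as a design weakness of minor to moderate weight. The protocol makes a subjective baseline score depend on a patient who already knows the arm, and it need not. The primary week-52 comparison keeps its 0.047 type I error.

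The exposed results are baseline comparability, change coefficients in the mixed model if pre-injury is included, the imputation and adjusted models through UCLA if that score also follows allocation, and, to a small degree (0.001 to 0.004 QALY under the assumed shifts), the cost-effectiveness baseline.

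For change coefficients the bias equals the recall difference. The documents give no data on its size. At 1 point the damage is slight and at 5 points it is serious, but both values are assumptions, and nothing in the protocol shows that a difference of any size will occur. The case for acting rests on the low cost of prevention and the lack of a later remedy.

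**What to change.** In Baseline data, state that the pre-injury DASH, EQ-5D-5L and UCLA activity score are completed at the consent consultation, after written consent and before the allocation is requested from the central coordinator. Align Recruitment, where randomization now follows consent directly.

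Do not discard scores that arrive later, as that would lose data needlessly. Record their completion date, flag them as post-allocation, and run a sensitivity analysis that leaves them out of any baseline adjustment or change analysis.

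The cost is a somewhat longer consent visit and a check by the trial worker that the forms are complete before the allocation is requested. The sample sizes stay at 163 and 124. A side benefit is that baseline data would then exist for patients who withdraw soon after randomization, which Participant withdrawal makes a condition for imputing their outcomes.

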### Primary outcome measure

The primary outcome is the DASH score at 52 weeks [3]. The DASH will also be assessed at pre-injury, 6, 12 and 26 weeks, and 2 and 5 years. The DASH score is a 30-item self-reporting patient-reported outcome measure specific for physical function and symptoms of the upper limb. Scores range from 0 (no disability) to 100 (most severe disability). The DASH score is validated for the target population [39] and has undergone cross-cultural adaptation in Danish, Swedish and Norwegian [40].

### Secondary outcome measures

Secondary outcomes consist of the DASH score, a self-reported measure of health-related quality of life (EQ-5D-5L), complication rates, visual analog scale (VAS) for pain from the arm, a functional outcome score (Constant-Murley), and anchor questions including clinical anchors, retrospective global transition questions and a binary repeat treatment question. Secondary outcome measures will be assessed at baseline, 6 weeks, 12 weeks, 26 weeks, and 52 weeks (Fig. 3):DASH score at earlier timepoints than 52 weeks (MIC [39], 7 and 10 respectively to age 18–64 and 65+)General health status questionnaire measured by EQ-5D-5L [41] (MIC [42], 0.074)Complications after treatment will be recorded and include local complications, early general complication, and mortality:Local complications: Infection (needing antibiotic treatment with or without debridement), nerve or vascular injury, surgical revision (due to implant malpositioning, hardware failure, aseptic loosening, or peri-implant fracture), and tolerance problems with a brace (discomfort resulting in non-compliance of wearing the braceEarly general complications needing hospitalization within 12 weeks from primary and secondary treatment [43, 44]:Major adverse cardiac events (MACE) including myocardial infarction, heart failure, cardiomyopathy and cardiac arrythmias.Other major adverse events include all-cause hospitalization other than the defined MACE.MortalityPain is assessed by using VAS. Patients are asked to assess their overall pain from the arm from 0 to 100 in a day (MIC [45], 16.55mm)Constant-Murley score [46] (MIC [39], 6.1). The subscales of strength and range of motion (ROM) will be depicted. ROM (flexion-extension) of the elbow will be recordedClinical anchor (CA) questions were presented with 5 response options (RO) and analyzed as a 5-point Likert scale:

Q: In general, would you say your health is?RO: Excellent, Very good, Good, Fair, Poor
*Q: How would you describe the results of the (operation/non-surgical treatment)?*
RO: Excellent, Very good, Good, Fair, Poor
*Q: How would you describe the function of your upper arm?*
RO: Excellent, Very good, Good, Fair, Poor
*Q: How would you describe the pain from your upper arm?*
RO: None, Mild, Moderate, Severe, ExtremeRetrospective global transition questions (RGTQ) presented with 5 response options and analyzed as a 5-point Likert scale:

*Q: Overall, how would you describe your general health now, compared to after the (operation / non-surgical treatment)?*
RO: Much worse, A little worse, About the same, A little better, Much better
*Q: Overall, how would you describe your upper arm now, compared to after the (operation/non-surgical treatment)?*
RO: Much worse, A little worse, About the same, A little better, Much better
*Q: How would you describe the change in physical function in your upper arm since after the (operation/non-surgical treatment)?*
RO: Much worse, A little worse, About the same, A little better, Much better
*Q: How would you describe the change in pain from your upper arm since after the (operation/non-surgical treatment)?*
RO: Much worse, A little worse, About the same, A little better, Much betterBinary repeat treatment question (BRT) presented with a binary response option:

*Q: With the knowledge and experience you have gained of the treatment; would you then choose the same treatment again for a similar fracture?*
RO: Yes, No

The DASH, EQ-5D-5L, and CA questions will be sent by email or mail and patients are asked to complete the questionnaires before visits. The questionnaires will be reviewed for missing data by a trial worker and patients will be assisted with completing the questionnaires if any data is missing, without interference from the medical staff. The trial worker collects the missing values before consultation with the physician. The physician then collects the additional outcome measures at the consultation and enters data directly into REDCap.

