## Abstract

**Background:**

The outcome of non-surgical treatment is generally good, but the treatment course can be long and painful with approximately a quarter of the patients acquiring a nonunion. Both surgical and non-surgical treatment can have disabling consequences such as nerve injury, infection, and nonunion. The purpose of the study is to compare patient-reported outcomes after surgical and non-surgical treatment for humeral shaft fractures.

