To our knowledge, four RCTs have been completed and all trials compared plate osteosynthesis to non-surgical treatment by DASH score and without distinction of age [13, 22–24]. Four RCT protocols [25–28] are registered in clinicaltrials.gov, WHO and ISRCTN registry. Two RCT protocols are comparing plate osteosynthesis to non-surgical treatment and the last two RCT protocols are comparing plate and nails to non-surgical treatment. Adults of all ages are included, except in one RCT protocol [27] that has an upper age limit at 65 years. Furthermore, in one already finished trial, the trial design had to be adjusted from an RCT to a prospective non-randomized comparative trial due to treatment allocation problems as there was a strong physician preference towards the surgical treatment option [29]. A Cochrane review could not demonstrate any difference in union rate between different surgical procedures (intramedullary nail and plate osteosynthesis) [30].

This emphasizes the need for a pragmatic approach of interventions by including usual care of surgical treatment, considering the influence of age as well as accepting early secondary surgery as a part of treatment to improve disability and function after 12 months.

The SHAFT protocol conforms with the Standard Protocol Items: Recommendations for Interventional Trials (SPIRIT) [31, 32].

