### Interim analyses

We will carry out two interim analyses after trial completion of 25% and 50% of the planned number of included patients, separately for the two age groups. We will use the O’Brien-Fleming rule [37] for determining appropriate significance levels for each analysis, which is determined by time of hypothesis testing (*n*=3) and the overall significance level of *α*=0.05. Under these assumptions, the significance levels are 0.0006 for the first interim analysis, 0.0151 for the second interim analysis, and 0.0471 for the final analysis. Interim analyses will be carried out for both the primary endpoint (DASH) and for serious complications (iatrogenic nerve injury, deep infection, major adverse cardiac events (MACE), other major adverse events, and death) and will be conducted by one-sided tests to determine if the improvement in DASH is significantly above 25 points, respectively if the complication rate is at least 20% higher.

A Data Monitoring Committee (DMC) has been organized to monitor and evaluate the data from the interim analyses. The DMC consists of five independent members including the patient representative (PR), two orthopedic researchers, an orthopedic surgeon, and a nurse.

In the event of one group having zero complications, the significance level cannot be computed by a cChi-square test, and the DMC will have to assess the data due to a statistical variation.

In the event of a patient sustaining several complications, the most severe complication will follow the patient. The complications are ranked in a hierarchy model describing the severity and are ranked from most severe to least severe: death, MACE, deep infection with debridement, other reasons for hospitalization, and iatrogenic nerve injury.

The interim analyses will be conducted by a biostatistician, blinded to the treatment allocation. Data will then be presented to the DMC, in means and proportions and be accompanied with confidence intervals. The DMC will have access to the data unblinded, and if at least one of those two conditions is fulfilled or a statistical variation has occurred at an interim analysis the DMC will be asked to investigate the results in detail and present their recommendation to continue or stop the trial. In the event of disagreement with a split decision (one or more casts a blank vote), the steering committee will be involved in discussing the stopping of the trial.

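### The early-complication rule counts all-cause hospitalisation over a window that restarts at secondary treatment, so observation time, and possibly the event itself, depends on crossover in one arm

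*Protocol article*

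**What the plan says.** The section Secondary outcome measures lists early general complications as those "needing hospitalization within 12 weeks from primary and secondary treatment". There are two categories besides mortality: major adverse cardiac events, and a remainder category, of which the protocol says "Other major adverse events include all-cause hospitalization other than the defined MACE". Planned admissions are not excepted, and secondary treatment is not defined.

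The section Interventions offers early crossover surgery only to patients allocated to non-surgical treatment, at 6-12 weeks in SHAFT-Y and 12-26 weeks in SHAFT-E. Background and rationale treats this surgery as belonging to the strategy: it speaks of "accepting early secondary surgery as a part of treatment to improve disability and function after 12 months".

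The section Interim analyses carries the category into the safety comparison of "serious complications (iatrogenic nerve injury, deep infection, major adverse cardiac events (MACE), other major adverse events, and death", with the criterion "respectively if the complication rate is at least 20% higher". A patient with several complications is recorded once, under the most severe, in the order "death, MACE, deep infection with debridement, other reasons for hospitalization, and iatrogenic nerve injury".

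**The concern.** In a comparison of two strategies, a harm endpoint should be counted by the same rule over the same time in both arms. Here the clock restarts when a patient receives secondary treatment. The protocol provides for such treatment in one arm only, so the non-surgical arm is watched for longer on average.

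The all-cause wording raises a second problem. Taken at its word, a SHAFT-Y patient admitted for crossover surgery at weeks 6-12 has a hospitalisation within 12 weeks of primary treatment, so a permitted step of the strategy is scored as a harm of it. The same wording might also take in the admission for the allocated operation, and the protocol does not settle this.

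The category is one component of the comparison that can prompt the monitoring committee to consider stopping. Because hospitalisation ranks above iatrogenic nerve injury, a patient with both is recorded under hospitalisation in that hierarchy.

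**Working it through.** The protocol gives no expected complication rate, crossover rate or observation time, so there is no figure of its own to reproduce.

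**Inputs**
- Window: 12 weeks from primary treatment and 12 weeks from secondary treatment (Secondary outcome measures).
- Crossover week T: 6-12 in SHAFT-Y, 12-26 in SHAFT-E (Interventions).
- Crossover share c: assumed 10-25%. The only nearby figure is in the Abstract, "approximately a quarter of the patients acquiring a nonunion". That is a nonunion rate, used here as an upper anchor.
- Background 12-week admission risk b: assumed 2-10%, equal in both arms.

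**Step 1, observed time.** The two windows overlap when T is below 12, so a crossover patient is observed for 12 + min(T, 12) weeks.
- SHAFT-Y: 12 + 6 = 18 weeks (crossover at week 6) to 12 + 12 = 24 weeks (week 12).
- SHAFT-E: 24 weeks throughout.

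The mean in the non-surgical arm is 12 + c × min(T, 12):
- SHAFT-Y, c = 10%: 12 + 0.10 × 6 = 12.6 to 12 + 0.10 × 12 = 13.2 weeks.
- SHAFT-Y, c = 25%: 12 + 0.25 × 6 = 13.5 to 12 + 0.25 × 12 = 15.0 weeks.
- SHAFT-E: 13.2 weeks at 10% and 15.0 weeks at 25%.

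The surgical arm has 12 weeks before any revisions, so the ratio is 12.6/12 = 1.05 to 15.0/12 = 1.25.

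**Step 2, second window alone (crossover admission not counted).** With a full further 12 weeks at the same risk, the non-surgical proportion is 1 − (1 − b)[(1 − c) + c(1 − b)]. Its excess over b is b × c × (1 − b).
- b = 2%, c = 10%: 0.02 × 0.10 × 0.98 = 0.2 percentage points.
- b = 10%, c = 25%: 0.10 × 0.25 × 0.90 = 2.25, about 2.3 points.

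For SHAFT-Y crossovers before week 12 the extra time is shorter, so these values are upper limits there.

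**Step 3, crossover admission counted, index surgical admission not.** The non-surgical proportion is 1 − (1 − b)(1 − c), an excess of c × (1 − b).
- c = 10%: 0.10 × 0.90 = 9.0 to 0.10 × 0.98 = 9.8 points.
- c = 25%: 0.25 × 0.90 = 22.5 to 0.25 × 0.98 = 24.5 points.

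The upper pair exceeds 20 points, which matters if the interim criterion is absolute; the protocol does not say whether it is absolute or relative. This scenario suits SHAFT-Y best, where the crossover admission falls inside the first window. In SHAFT-E, apart from crossover at week 12, the admission can count only as the start of the second window, which is the same footing as the index operation has in the first.

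**Step 4, both kinds of admission counted.** Nearly every surgical patient admitted for the allocated operation then has an event, against c plus background in the other arm. The imbalance reverses.

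**Step 5, after the change proposed below.** Every patient has the same planned window (ratio 1.00), and with equal underlying risk the expected difference is 0.

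**The case against.** The best reply is that the all-cause line stands under headings that speak of complications after treatment. On that reading an admission for either operation is the treatment, and secondary treatment only opens a window. The local-complications list supports this: it names surgical revision for implant-related reasons and does not mention crossover surgery. Nor does the protocol say that crossover surgery needs admission. This stands as evidence of intent, and it means that scoring crossover admissions as events is one reading and not a stated rule. But the category that sites would code says all-cause, and the two readings differ by up to about 25 points.

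It can also be said that an article leaves event-classification detail to fuller documents. That would answer a silence. The all-cause scope and the restarting window are both stated here.

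The second window has a purpose: it captures harm after crossover surgery, which in SHAFT-E a single 12-week window would almost entirely miss. That is a good reason to keep those counts, but not to base the between-arm comparison on unequal time.

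Finally, meeting the interim criterion stops nothing automatically. The committee sees unblinded data and is asked to look into them, and the Abstract promises that all complications will be reported, so nerve injuries and infections should remain visible elsewhere. This limits the consequence.

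A reader might go further and infer that planned crossovers certainly count as harm of non-surgical care and so hide an excess of surgical complications, perhaps reversing its sign. The documents do not support that. It applies the literal wording to one arm only, and any such example needs complication and crossover rates that the protocol does not give.

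**Conclusion.** The point holds in a limited form. What is certain from the text is that observation time depends on post-randomisation treatment, and that permitted crossover makes it longer in the non-surgical arm: by 5-25% at an assumed 10-25% crossover, before any revisions in the surgical arm. If secondary treatment includes revisions, they would narrow the gap somewhat. The effect of this on event rates is small, about 0.2-2.3 percentage points for an assumed background risk of 2-10%.

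The larger issue is the missing exception for planned admissions. It is worth about 9-25 points against the non-surgical arm if only crossover admissions count, and it turns against the surgical arm if index admissions count as well. The size and the sign both depend on how sites read the wording, so no direction of bias can be claimed. The crossover share is the weakest assumption: the upper value comes from a nonunion rate, whereas the crossover criteria are pain, instability and brace intolerance. Because the category enters the interim complication test, the wording should be settled before the first interim analysis.

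**What to change.** - State that admissions for the allocated treatment and for protocol-permitted crossover surgery are not events in either arm, whereas complications arising from them are.
- Define secondary treatment, including whether revisions after allocated surgery belong to it.
- Base the between-arm comparison, at interim and final analysis, on one common window from randomisation. Week 52 would serve: the latest permitted crossover plus 12 weeks is 26 + 12 = 38 weeks. Interim data would need the same treatment in both arms for patients who have not yet reached the end of the window.
- Keep the counts within 12 weeks of each treatment as a descriptive table.

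The cost is a change of wording; visits to week 52 are already planned. The drawback is that a longer window takes in some unrelated admissions, particularly in SHAFT-E. These are expected equally in both arms, so they dilute the comparison without tilting it, and the descriptive table still shows the early, treatment-related picture.
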